### Data collection and management

#### Data collection

This trial uses paper data collection forms, electronic data capture through STaRS, and data abstracted from the participant’s electronic medical record.

The STaRS home page provides all users the same login that, upon validation, directs them to the appropriate section of the application according to login credentials. PMs enter baseline data, including the exam screening form, into customized logic-based electronic forms that provide validation checks to ensure participant eligibility prior to allocation.

Electronic data capture is used to collect PROs at 2, 4, 6, and 12 weeks from allocation (Table 2). Participants are directed to the outcome assessments. Many features were implemented to provide participants with a self-managed experience while collecting study data at respective intervals over the 12-week study period. Participants may complete the assessment from any device capable of supporting an internet connection and web browser. If a participant forgets or would like to change their password, a link is provided that sends them a temporary password to their email address. At the time of the next login with the temporary password, STaRS will prompt the user to define a new password for future use. Within the STaRS application, participants may also update their contact information at any time.

Outcome measures are collected in a linear manner across all time points. Primary outcome measures are required variables and must be completed as a whole, whereas secondary outcome measures may be skipped by the participant. Programmatic review prompts the users after each assessment for any missing variables and asks them to review and complete them before moving onto the next measure. A visual progress bar is provided at the bottom of the page to inform users of overall percent completed.

STaRS sends an email at pre-programmed intervals to remind participants to complete the online assessments. Outcome assessments are available to complete for a window of 6 days for weeks 2 and 4, and 14 days for weeks 6 and 12. Automated emails are programmed to be sent the day the window opens for the respective time point. An additional email will be sent by STaRS if the participant has not completed the assessment by the actual due date. To augment STaRS automated emails, the PM personally contacts each participant by text message, email, or telephone during the window for each assessment. Participants can inform the site PM if they are unable to access STaRS or complete the assessment for various reasons. All contact with participants is documented by the site PM within STaRS.

If a participant does not complete an assessment within the designated window (Table 2), a PM will attempt to collect the primary outcome measures using a computer-assisted telephone interview. A PM will attempt to collect the week 2 and 4 assessments within 3 days, and the week 6 and week 12 assessments within 7 days of the assessment expiration dates.

For participants in the group that also receive chiropractic care, the DC completes a paper data collection form for each study visit that details the type of spinal manipulation performed including the anatomical region, and other therapeutic procedures used with the corresponding diagnosis (ICD-9) and procedural (CPT) codes. The PM carefully tracks the number of study visits per patient that occur in the 6-week period and manages documentation for study visits. During the active care phase of the trial, PMs enter data from the study treatment forms into customized electronic forms. Data entry errors and change requests are submitted through a module within STaRS that provides an audit trail of who altered specific data elements and when they were altered.

To document UMC received for LBP and to explore healthcare utilization for LBP, information from healthcare provider visits for LBP that occur during the 12-week study period is abstracted from the participant’s electronic medical record. Data abstracted includes reason for visit, provider type(s), diagnoses, procedures conducted, and prescribed medications.

The dual purpose of the STaRS application allows for trial management tools. STaRS is programmed to produce reports to allow study staff to monitor participants through all phases of the study. Specific reports available to study staff include a screening report, which provides the number of participants screened as well as the reasons for exclusion, and a tracking report, which allows the user to view individual participant information such as date of important study visits, allocation, and the status of each outcome assessment. PMs can monitor trends with respect to missed outcomes. PMs also enter adverse events and protocol deviations into STaRS, which is programmed to provide emails to specific study investigators as well as research staff. This feature allows for central investigator oversight, which is especially important given the multiple site locations.

#### Data management and security

The STaRS application is 21 CFR part 11 compliant and integrated with a Central Participant Database and a Project/Users Permissions System to control project personnel access to web modules. PCCR registered the backtoaction.org site secured with Certified Secure Socket Layers (SSL) 128-bit encryption, hosted (IIS V6.0), and maintained by Palmer College of Chiropractic Information Services department. The web programmer developed the application in ASP.NET v4.0 in C# and Structured Query Language (SQL) using Microsoft Visual Studio 2010. All data are stored on an internal Microsoft SQL Server 2014. Only select study personnel have access to data via Microsoft SQL Server Management Studio 2014. All PCCR servers reside behind a stateful firewall with permissions determined by Active Directory.

The data core manager will perform a soft lock of the database (Microsoft SQL Server) and write programs in SAS System for Windows (Release 9.3) using SAS ACCESS in order to perform data cleaning procedures of range and consistency checks. Once all data edits are recorded and performed, the data core manager will coordinate with the programmer to perform a final lock removing all access to the database to ensure that no further changes to the data can be made. Final analyzable dataset(s) and the data dictionary will be created from the final locked database.

### Statistical methods

The data will be analyzed using an intention-to-treat approach in which participants will be analyzed according to their original treatment allocation. All observed data will be used in the analyses. Data analyses will be performed using SAS/STAT (Release 9.3) (SAS Institute Inc., Cary, NC).

#### Primary data analysis and sample size

The co-primary outcome variables (RMDQ and the NRS for LBP intensity) will be modeled with linear mixed effects regression over baseline and weeks 2, 4, 6, and 12. We will assume group means are the same at baseline, and include terms in the model for time (as a categorical variable), site, site-by-group, time-by-group, and site-by-time-by-group interactions, and the variables in the minimization algorithm. The covariance structure will be chosen by comparing the maximized log-likelihoods and the Bayesian information criteria for several covariance pattern models against the unstructured covariance. Diagnostics of the conditional predicted values and conditional residuals will be used to assess the assumption of normality and fit for each model.

The main results will be based on the final models for the co-primary outcome variables at the end of the active care phase (6 weeks). If the site-by-time-by-group interaction is significant at the 0.05 level, results will be reported by site. A *p*-value ≤ 0.025 will be used to determine if between group differences are statistically significant.

Because the patient populations at the three sites are different, we calculated a sample size of 106 per group for each site to provide adequate power to detect clinically important differences between groups at each site. The sample size estimates were obtained using a significance level of 0.025 to account for 2 primary outcome variables. The estimates of standard deviation (5.4 for the RMDQ and 2.0 for the NRS for average pain intensity over the past week) come from our pilot study [28]. This provides 80 % power to detect a 2.4 between group difference on the RMDQ and 92 % power to detect a 1.2 difference on the NRS. In the pilot study, there was 13 % and 11 % missing data in the UMC plus chiropractic care group at the week 2 and 4 assessment periods, respectively, but 39 % and 37 % in the UMC alone group. We increased the sample size to 125 per group at each site, assuming we would be able to keep our loss to follow-up at the week 6 endpoint at or below 15 %, due to the implementation of intensive follow-up procedures.

Secondary evaluations of the final models will compare group differences at week 12 to ascertain if the pattern seen at week 6 remains after the active care phase. Group differences will also be reported for week 2 and 4 to compare to the results of the pilot study. Secondary analyses will compare the percentage of patients with clinically meaningful improvement of at least 30 % relative to baseline at the week 6 endpoint on the co-primary outcome variables [49]. General estimating equations with a working covariance matrix will be used to estimate the differences in proportions between groups at each time point, with terms in the model for time (as a categorical variable), group, site, site-by-group, and time-by-group interactions, and the minimization variables. Consistent with the recent NIH Task Force recommendations [50] for a minimum dataset for chronic LBP, we will conduct an exploratory analysis over a range of improvement levels.

Two approaches to sensitivity analyses will be used to examine the possible effects of missing data on the results obtained from using all observed data for the co-primary outcome variables. Prior to conducting the sensitivity analyses, baseline variables that are predictive of missing outcomes will be identified with logistic regression models. The first approach will be under the assumption that data are missing at random and will use the Markov chain Monte Carlo method to impute missing values for each of the primary outcome variables based on the final mixed model covariates, the observed outcome variable at baseline and weeks 2, 3, 6, and 12, and the baseline variables predictive of missing data. The resulting datasets for each of 20 imputations will be analyzed with the linear mixed effects models that are fit with all observed data and the results will be combined. The second approach will be under the assumption that data are missing not at random. It will follow the pattern mixture approach described by Carpenter and Kenward [51] by first imputing missing values as described above for the missing at random approach and then for each participant in each treatment group for each imputation. The imputed observation will be decreased by different amounts representing different patterns of responses. The resulting datasets for each pattern will be analyzed and the estimates combined as described above. If results differ between the analysis of the observed data and that based on imputed full datasets under different missingness assumptions, multiple sets of results will be reported.

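### The primary model omits site-by-time, so the test that triggers by-site reporting also reacts to site differences in recovery that both arms share

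*Protocol article*

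**What the plan says.** All of this is in the Protocol article, section Primary data analysis and sample size. RMDQ and NRS are each "modeled with linear mixed effects regression over baseline and weeks 2, 4, 6, and 12", so baseline is one of five modelled responses. On the fixed effects the article states "We will assume group means are the same at baseline", and says the analysts will "include terms in the model for time (as a categorical variable), site, site-by-group, time-by-group, and site-by-time-by-group interactions", together with the minimization variables. Neither site-by-time nor a group main effect is listed.

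The decision rule is "If the site-by-time-by-group interaction is significant at the 0.05 level, results will be reported by site". The sample size paragraph opens its reasoning with "Because the patient populations at the three sites are different" and sizes each site separately. Statistical methods names SAS/STAT as the software. The article does not say how group is coded or how the baseline assumption is imposed.

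**The concern.** A three-way interaction isolates treatment heterogeneity only when every two-way term inside it is also in the model. Here one is absent. If patients at one site improve faster in both arms, that pattern has nowhere to go except the three-way term, although the treatment effect is the same everywhere. The article itself expects the sites to differ and admits acute, subacute and chronic pain. The minimization variables, pain duration among them, are listed without a time interaction, so they do not absorb the pattern.

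The test decides whether the trial gives one answer or three for each co-primary outcome. The list also reaches further: the multiple imputation uses the final model's covariates, and the continuous secondary outcomes are modelled the same way.

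The second issue is the site-by-group term that is not crossed with time. With an ordinary allocation variable it acts at baseline too, which does not fit equal baseline means.

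**Working it through.** **Inputs from the article:** 5 time points, 3 sites, 2 groups (30 cells); 106 evaluable per group per site; SD 5.4 (RMDQ) and 2.0 (NRS); trigger level 0.05.

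**The plan's own figures.** It gives none for the trigger. The inflation reproduces: 106/0.85 = 124.7, so 125. At 106, two-sided 0.025, RMDQ power is Φ(2.4/(5.4·√(2/106)) − 2.241) = Φ(3.236 − 2.241) = 84% (stated 80%). The NRS figure is Φ(4.368 − 2.241) = 98% (stated 92%). The stated powers are conservative, and nothing below depends on them.

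**Degrees of freedom of the trigger** (rank of the 30-cell design without and then with the three-way term):

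| Terms | Group coding | Ranks | df |
|---|---|---|---|
| As listed | SAS class variable | 14 → 30 | 16 |
| As listed | class variable, reference level at baseline | 13 → 27 | 14 |
| Add group and site-by-time | SAS class variable | 22 → 30 | 8 |
| Add site-by-time, keep site-by-group | post-baseline only | 21 → 27 | 6 |
| Add site-by-time, drop site-by-group | post-baseline only | 19 → 27 | 8 |

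In the first two rows, 8 of the df are site-by-time. The full heterogeneity test over follow-up has (3 − 1) × 4 = 8 df. In the fourth row, site-by-group takes out the 2 df for heterogeneity that is constant over time.

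**How often the trigger fires with no treatment heterogeneity.** My assumptions: complete data, known covariance, the same treatment effect at each site, and one site improving by d more in both arms. The shift is either constant from week 2 or rises linearly to week 6 and then holds. Correlation is 0.5 throughout, or 0.4 baseline to follow-up and 0.65 among follow-ups.

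Under class coding with common correlation ρ, the noncentrality is

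λ = 2 · n · Σ(site deviations)² · Σ(time deviations)² · d² / (σ²(1 − ρ)).

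For one faster site, Σ(site deviations)² = (2/3)² + 2(1/3)² = 2/3. For a constant shift, Σ(time deviations)² = 0.8² + 4(0.2²) = 0.8. With n = 106, σ = 5.4, ρ = 0.5 and d = 1:

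λ = 2 × 106 × (2/3) × 0.8 / (29.16 × 0.5) = 113.07/14.58 = 7.75.

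Against the 16-df critical value of 26.30, the rejection probability is 0.340. For d = 1.5 and 2.0, λ is 17.45 and 31.02, giving 0.747 and 0.968. For NRS, d = 0.5, λ = 113.07 × 0.25/(4 × 0.5) = 14.13, giving 0.629.

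Range over both correlation patterns and both time profiles:

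| Shift d | 16 df | 14 df | Site-by-time included |
|---|---|---|---|
| RMDQ 1.0 | 0.222–0.340 | 0.152–0.277 | 0.05 |
| RMDQ 1.5 | 0.522–0.747 | 0.334–0.636 | 0.05 |
| RMDQ 2.0 | 0.835–0.968 | 0.603–0.916 | 0.05 |
| NRS 0.5 | 0.419–0.629 | 0.268–0.521 | 0.05 |
| None | 0.05 | 0.05 | 0.05 |

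If instead the three sites are spread evenly (0, d/2, d; rising shift, correlation 0.5), the 16-df rates for RMDQ are 0.24, 0.55 and 0.86. At d = 1 the range over correlation 0.3 to 0.7 is 0.17 to 0.41.

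**Other codings.** With ordinary 0/1 reference coding (8 df), the same evenly spread pattern gives 0.16, 0.34 and 0.60. With sum-to-zero coding and balanced data the rate stays at 0.05. With one hand-made 0/1 post-baseline indicator the term has 6 df, and a constant shift leaves its test at 0.05. That coding forces the UMC arms onto one time course, however. A 1.5-point shift then moves the site-specific week-6 RMDQ differences by about −0.8 at the faster site and +0.4 at the other two.

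**Baseline.** With an ordinary class variable the listed terms leave three free baseline group differences, one per site. With group coded post-baseline only they leave none. Under class coding, deleting site-by-group alone changes nothing (the rank stays 30), because time-by-group and the three-way term also include baseline.

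**The case against.** The strongest defence is that the sentence states the equal-baseline assumption before it lists the terms. The missing group main effect, which the responder model in the same section does include, suggests a deliberate constrained longitudinal model. That is a fair reading. Under it the baseline conflict disappears and the trigger has 14 df, not 16. It does not supply site-by-time, so the trigger problem remains.

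Second, the article sizes no site difference in recovery. Different populations need not recover differently, and differences in level are absorbed by the site term. This stands: the rates above are conditional.

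Third, over-firing leads only to by-site reporting, for which each site was sized, and under class coding the treatment contrasts are unbiased. This limits the harm but does not make the rule test what it is meant to test.

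A reader might infer more than the article supports:

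- **That the baseline assumption is broken and power is lost.** A free baseline raises the week-6 variance by 1/(1 − ρ²), which is 1.33 at ρ = 0.5 (1.10 at 0.3, 1.96 at 0.7), and site-level RMDQ power is then 84% instead of 93%. That needs ordinary class coding, and 84% still exceeds the planned 80%. Nothing promised is forfeited.
- **That site estimates will be biased by −0.8 and +0.4.** That needs hand-made indicators and cannot occur together with the 16-df test. The article commits to neither.

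**Conclusion.** The point holds for the trigger. Under SAS class coding, and under the post-baseline class coding that best honours the stated assumption, the listed terms make the by-site rule respond to recovery differences common to both arms. With a common treatment effect and one faster site, it fires about 15–34% (RMDQ shift 1.0), 33–75% (1.5), 60–97% (2.0) and 27–63% (NRS shift 0.5) of the time, where 5% is intended. These figures rest on assumed shifts, correlations and complete data. With no site difference in recovery the level is correct.

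The site-by-group point is conditional. The term conflicts with equal baseline means unless group is coded post-baseline only. Under that coding it leaves the baseline alone but takes 2 df of time-constant heterogeneity out of the trigger, leaving 6 of 8 once site-by-time is added. It is unhelpful under either coding. The article does not support a claim of a broken model, of power lost against plan, or of biased estimates.

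**What to change.** State the fixed effects as time, site, site-by-time, group-by-post-baseline-time, site-by-group-by-post-baseline-time and the minimization variables, with all group terms zero at baseline. Drop the separate site-by-group term. State that the by-site trigger is the 8-df test of site-by-group-by-post-baseline-time.

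This costs a sentence or two in the analysis plan before the final database lock, and no new data. The revised model has 27 cell-mean parameters, no more than the listed terms give under either class coding (30 or 27). The same wording should carry through to the imputation model and the continuous secondary outcomes, which take their terms from this list.

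### By-site reporting of the week-6 result is triggered by an interaction test over all visits, and the site comparisons that follow are judged at a level set for two outcomes only

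*Protocol article*

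**What the plan says.** All of this stands in the protocol article, section Primary data analysis and sample size.

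- **Model.** Each co-primary outcome (RMDQ and NRS average pain) "will be modeled with linear mixed effects regression over baseline and weeks 2, 4, 6, and 12", with time categorical. Besides time, the terms are "site, site-by-group, time-by-group, and site-by-time-by-group interactions, and the variables in the minimization algorithm". On baseline: "We will assume group means are the same at baseline".
- **Main result.** The group difference at week 6, from the final model for each outcome, judged at p ≤ 0.025.
- **Site rule.** "If the site-by-time-by-group interaction is significant at the 0.05 level, results will be reported by site".
- **Level.** The sample size uses a "significance level of 0.025 to account for 2 primary outcome variables". No other threshold is given for comparisons within a site.
- **Site sample size.** Because the site populations differ, "we calculated a sample size of 106 per group for each site to provide adequate power"; this becomes 125 per group per site after allowing for 15% loss.

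The section does not say what happens to the pooled week-6 difference once results are reported by site.

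**The concern.** A rule that decides whether the week-6 result is presented pooled or by site should ask whether sites differ at week 6. The three-way interaction asks whether they differ in any way across the follow-up visits. Sites that recover at different speeds but agree at week 6 can set it off. Depending on how the term is coded, sites that differ by the same amount at every visit, week 6 included, may hardly move it.

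Once it fires, each outcome gives three site comparisons instead of one pooled comparison. The 0.025 level divides 0.05 between two outcomes and leaves nothing for three sites. At stake are which analysis carries the primary conclusion and how often a false site-level claim is made.

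**Working it through.** **The plan's own figures.** 0.05/2 = 0.025. 106/0.85 = 124.7, so 125 per group; 125 × 2 × 3 = 750. These reproduce. The stated per-site power does not: a two-sided two-sample calculation at 0.025 with 106 per group gives about 84% for an RMDQ difference of 2.4 (SD 5.4; stated 80%) and 98% for an NRS difference of 1.2 (SD 2.0; stated 92%). That is a separate, conservative discrepancy, and nothing below depends on it.

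**Inputs.** From the article: 3 sites, 106 evaluable per group per site, four post-baseline visits, 2 outcomes, trigger at 0.05, group comparisons at 0.025 (taken as two-sided). Assumed: equal correlation ρ between visits, known variances, and a correlation between outcomes of 0 to 0.7.

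**Degrees of freedom.** With baseline means constrained equal, group effects can differ among 3 sites at 4 visits: 2 × 4 = 8 df. If the separate site-by-group term takes up the part constant over visits, 2 × 3 = 6 df remain. The article does not settle which, so both are shown.

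**Trigger.** Let one site's group difference depart from the other two by d SD. Define K = d² × (106/2) × (2/3). The noncentrality parameters are:

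- difference at week 2 only, 8 df: K × [1/(1 − ρ)] × [1 − ρ/(1 + 3ρ)]
- difference at week 2 only, 6 df: 0.75K/(1 − ρ)
- constant difference, 8 df: 4K/(1 + 3ρ)
- constant difference, 6 df: 0
- 2-df week-6 contrast: K if the difference is present at week 6, otherwise 0

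*Week 2 only, d = 0.3, ρ = 0.65.* K = 0.09 × 53 × 2/3 = 3.18. For 8 df: 3.18 × 2.857 × 0.780 = 7.08 against a critical value of 15.51, so 42%. For 6 df: 3.18 × 0.75/0.35 = 6.81 against 12.59, so 46%. The week-6 contrast fires in 5%. At ρ = 0.4 the two forms give about 26% and 27%; at ρ = 0.8, about 69% and 73%. With all visits equally correlated, a difference at week 12 only gives the same values.

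*Constant over visits, d = 2.4/5.4 = 0.44, ρ = 0.6.* K = 6.98. The 6-df form fires in 5%. The 8-df form has noncentrality 6.98 × 4/2.8 = 9.97 and fires in 59% (49% at ρ = 0.8, 71% at ρ = 0.4). The week-6 contrast fires in 65%.

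**Error rate.** If all six site comparisons are reported and independent, 1 − 0.975⁶ = 14.1%; with correlated outcomes, about 12% to 14%. If one outcome triggers, three site tests and one pooled test remain: 1 − 0.975⁴ = 9.6% under independence. Simulation of the whole rule (200,000 trials, no group effect at week 6) gives:

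| Situation | 8 df | 6 df |
|---|---|---|
| Global null | 6.5% to 7.5% | 5.0% to 6.5% |
| One site differs by 0.44 SD at week 2 only, both outcomes | about 13% | about 12% |

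Testing only the pooled differences gives 4.2% to 4.9%. Under the global null at least one outcome triggers in roughly 9% of trials, which is why the overall inflation is small.

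**The case against.** The strongest reply is that site-level inference is a design aim. The article says the populations differ and sizes each site separately, so 0.025 may be meant to cover two outcomes within each of three distinct comparisons. It nowhere promises 5% error across sites, and whether alpha must be shared across distinct populations is debatable. This stands as a reason to let the sponsor choose the status of site results. It does not rescue the trigger, which is mismatched to week 6 whatever level is used, and sizing each site at 0.025 is not itself multiplicity control.

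Three stronger readings are tempting and are not supported:

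- **The pooled result is dropped, so the trial may end without one primary answer.** The site rule directly follows the sentence on the main results, so replacement is a natural reading, but the text does not say it. What can be said is that the status of the pooled result is left open.
- **The trial's error rate is 12% to 14%.** That needs both outcomes to trigger nearly every time because of real differences at other visits, with no effect at week 6 at any site.
- **Adjusting for sites breaks the stated RMDQ power.** At 0.05/6 an unadjusted two-sample calculation gives 71.6% (NRS 95.5%). The planned model uses baseline. If 5.4 is an unadjusted SD, which is not stated, assumed baseline correlations of 0.3, 0.4 and 0.5 give about 77%, 81% and 86%. A shortfall is not established.

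**Conclusion.** The point holds in limited form and should be fixed. This is not an omission left to an analysis plan: the article fixes the trigger, its level and its consequence. The trigger responds to site differences away from week 6 and, in its 6-df form, is blind to a constant one. The 0.025 level makes no allowance for three sites.

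The mismatch is the larger part: about 42% to 46% against 5% for a 0.3 SD week-2-only difference. The error inflation is modest under the global null and substantial only when by-site reporting becomes regular. The sizes rest on assumed correlations, known variances and 106 evaluable per group per site. The direction of the mismatch does not depend on those values.

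**What to change.** Change the wording before group codes are released to the analysts:

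1. State that the pooled week-6 difference for each co-primary outcome, at 0.025, is the primary result in every case. With 3 × 106 = 318 per group its power exceeds 99.9% for either stated difference, so no extra participants are needed.
2. Assess heterogeneity with the 2-df site-by-group contrast at week 6, and state its coding.
3. Report site estimates with confidence intervals as supportive, with no confirmatory claim. Alternatively, to serve the per-site aim, allow site claims for an outcome only after its pooled test succeeds, with adjustment (for example Holm) across the three sites within that outcome's 0.025.

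Two partial remedies fall short. Moving the trigger to week 6 while leaving site tests at 0.025 raises global-null error to about 10%, because it selects the trials whose week-6 site estimates lie furthest apart. Adding ungated Holm-adjusted site claims beside two pooled tests that already spend the full 0.05 gives about 7.5% to 8.5%.

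The cost is that site-level claims become supportive or face a stricter threshold.

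### The stated site-level power (80% for RMDQ, 92% for NRS) does not follow from the printed sample size, SDs, differences and alpha, which give about 84% and 98%

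*Protocol article*

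**What the plan says.** The Protocol article sets out the calculation in one paragraph under Primary data analysis and sample size, and gives every input needed to repeat it.

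- Size: "we calculated a sample size of 106 per group for each site".
- Alpha: the estimates were "obtained using a significance level of 0.025 to account for 2 primary outcome variables".
- SDs, taken from the pilot study: "5.4 for the RMDQ and 2.0 for the NRS for average pain intensity over the past week".
- Results, for disability and then for pain: 80% "power to detect a 2.4 between group difference on the RMDQ and" "92 % power to detect a 1.2 difference on the NRS".

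The number is then raised to 125 per group per site to allow for up to 15% loss at week 6. The paragraph mentions no correlation, baseline adjustment, clustering or variance inflation. The purpose given is adequate power at each site separately, because the three patient populations differ.

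**The concern.** A power statement should follow from the inputs printed beside it. Here both figures come out higher when recalculated, and by different amounts, so one common cause is unlikely.

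The statement supports the choice of site size for both co-primary outcomes, and results are to be reported by site if the three-way interaction is significant. A reader judging a site result will naturally look to these figures for what the design could detect, although the article does not itself assign them that use. On the NRS, the possible explanations mean different things:

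- the printed power is simply too low;
- the design reaches a difference of about 1.0 rather than 1.2;
- the planning SD was about 2.4 rather than 2.0.

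The reader cannot tell which applies.

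**Working it through.** **Inputs** (all from Primary data analysis and sample size): n = 106 per group; alpha = 0.025; RMDQ difference 2.4, SD 5.4; NRS difference 1.2, SD 2.0. Sidedness is not stated; two-sided is assumed first and one-sided is tried below.

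**The part that reproduces.** 106 / (1 − 0.15) = 124.7, rounded up to 125 per group; 125 × 2 × 3 = 750. So 106 is the evaluable number per group that was intended.

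**Power, normal approximation.** Power = Φ(δ / (σ√(2/n)) − z), with z = 2.2414 for two-sided 0.025 and √(2/106) = 0.13736.

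- RMDQ: standard error 5.4 × 0.13736 = 0.7418; 2.4 / 0.7418 = 3.236; Φ(3.236 − 2.241) = Φ(0.994) = 84.0%.
- NRS: standard error 2.0 × 0.13736 = 0.2747; 1.2 / 0.2747 = 4.368; Φ(4.368 − 2.241) = Φ(2.127) = 98.3%.

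**Power, exact.** The noncentral t with 210 degrees of freedom and noncentrality 3.236 and 4.368 gives 83.5% and 98.2%. The stated values are 80% and 92%.

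**Other readings** (exact t):

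| Reading | RMDQ | NRS |
|---|---|---|
| Stated in the article | 80% | 92% |
| n = 106, two-sided 0.025 | 83.5% | 98.2% |
| n = 106, one-sided 0.025 | 89.6% | 99.2% |
| n = 106, two-sided 0.0125 | 76.2% | 96.7% |
| n = 90 (if 106 were the number before losses), two-sided 0.025 | 76.4% | 96.0% |
| n = 125, two-sided 0.025 | 89.5% | 99.3% |
| n = 106, two-sided 0.025, least favourable rounding (2.35 / 5.45; 1.15 / 2.05) | 81.0% | 96.5% |

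**Can one changed input explain both?**

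- Alpha: 80% on the RMDQ needs about 0.018; 92% on the NRS needs about 0.0035.
- Sample size: n = 2(σ/δ)²(z + z_power)². RMDQ: 2 × 5.0625 × (2.2414 + 0.8416)² = 96.2, so 97 (98 by exact t). NRS: 2 × 2.7778 × (2.2414 + 1.4051)² = 73.9, so 74 (76 by exact t). Neither is 106.
- Variance factor: the SDs needed at n = 106 are 5.63 and 2.38, so the factors would be (5.63/5.4)² = 1.09 and (2.38/2.0)² = 1.42. These are not a common inflation.

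**What does match at n = 106 and two-sided 0.025:**

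- Printed SDs with differences of 2.3 and 1.0: 80.0% and 91.6%. The normal-approximation sample size for 2.3 is 2 × (5.4/2.3)² × 9.505 = 104.8, so 105, close to the printed 106.
- Printed differences with SDs of 5.6 and 2.4: 80.5% and 91.6%.

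**The case against.** The best case for leaving the text alone has three parts.

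First, the RMDQ gap may be little more than rounding. All inputs are given to one decimal, and a difference of 2.35 with an SD of 5.45 gives 81.0%, within a point of the stated value. This stands: the RMDQ mismatch is weak evidence on its own. It does not carry over to the NRS, where the least favourable rounding still gives 96.5%.

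Second, the error is harmless. On the printed inputs each site has more power than claimed. If larger SDs were in fact used, the stated powers are about right. No reading shows a shortfall, no decision rule depends on the figures, and recruitment closed with all 750 allocated. This also stands, and it makes the point a reporting correction rather than a threat to validity.

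Third, the article nowhere says that these differences will be used to interpret a null result at a site, so misreading of smaller effects is conjecture. That is fair, and the conclusion does not depend on it.

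None of this makes the sentence correct. The inputs and the result stand in the same paragraph and disagree, so an unseen analysis plan would not cure it.

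**Conclusion.** The concern holds. With 106 per group, the printed SDs and differences, and a two-sided t-test at 0.025, power is 83.5% for the RMDQ and 98.2% for the NRS, against 80% and 92% stated. For the NRS the false-negative rate is 1.8% rather than 8%; put the other way, 92% power corresponds to a difference of 1.01, not 1.2. The NRS discrepancy survived every alternative tried (sidedness, alpha, sample size, rounding). The RMDQ discrepancy holds on the figures as printed but could be mostly rounding.

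The assumptions are a two-sided test, equal allocation and a simple comparison of two means; one-sided testing widens the gap. The close match with differences of 2.3 and 1.0 suggests that the printed differences may be the misprint, but the article does not settle this. The sample size is not called into question.

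**What to change.** Go back to the original calculation, establish which figure was misprinted, and correct that one sentence. State at the same time that the test is two-sided, if it is. The correction is one of three:

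1. If the SDs and differences are right, restate the powers as 84% for an RMDQ difference of 2.4 and 98% for an NRS difference of 1.2.
2. If the powers and SDs are right, restate the differences as 2.3 and 1.0.
3. If the powers and differences are right, restate the SDs actually used (about 5.6 and 2.4) and reconcile them with the pilot-study source given for them.

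The cost is one lookup and one edited sentence. The 106 evaluable and 125 enrolled per group per site, and the total of 750, do not change.
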